### Handling of missing data

If only one component of a multiple component score (such as TRS part A, B, or C; QUEST part A to E; or SF-36 item groups 3 to 11) is incomplete, the missing item value(s) will be imputed using the most frequent (mode) response to this item in the entire group at the corresponding time point.

If a value measured after DBS is completely missing, the patient will be excluded from the main analysis of the corresponding endpoint. However, in order to guard against bias, a sensitivity analysis is performed reincluding these patients and using multiple imputation methods.

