Only if implantation criteria are fulfilled, i.e., both leads are placed as described above and proper lead location is confirmed via stereotactic X-ray or postoperative CT scan, are patients included at 3MFU into the double-blinded, randomized phase of the study. Patients are randomized into two groups (group 1: VIM-DBS followed by PSA-DBS; group 2: PSA-DBS followed by VIM-DBS). The crossover is double-blinded (neither the patient nor the treating neurologist knows which area is stimulated in which period) and lasts for 4 months (2 months on each treatment). A programming visit (PV) is performed at the beginning of each period (at 3MFU and 5MFU) and the best clinical stimulation parameters of the respective contact are determined (i.e., best tremor suppression with no or tolerable side effects). The stepwise increase of current of the electrode contacts in the crossover phase yields a better understanding of the therapeutic windows (i.e., range between effect and side effect) of the two target areas. Double-blinding is also maintained during the programming visit, as adjustment of stimulation parameters is performed by an independent investigator (programmer) as instructed by the blinded rater. An evaluation visit (EV) is performed after each group (EV1 at 5MFU and EV2 at 7 MFU). As the effects and side effects are known to be immediate (although not systematically investigated for VIM-DBS), a longer washout phase between the two crossover phases is not necessary. After the crossover phase, the contact with the best effect and fewest side effects or more complex stimulation paradigms (such as double monopolar or bipolar configurations) can be freely chosen for further treatment until 12MFU.

For study question 1, the change from preoperative to postoperative TRS during 2 months of PSA stimulation will be analyzed. Therefore, the data will be pooled from the EV at 5MFU and 7MFU depending on randomization.

Patients without electrode placement according to the implantation criteria (see above) but with electrodes bilaterally located in the PSA will be stimulated in the PSA directly after implantation, evaluated at 3MFU and 12MFU, and will be excluded from the comparison between PSA and VIM. For the longitudinal PSA effect, 3MFU data from these patients will be pooled with 5MFU and 7MFU data from the randomization group, respectively.

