### Statistical analysis

For study question 1, the reduction of tremor due to PSA-DBS is calculated by subtracting the TRS score at baseline from the score obtained after the 2 months of continuous PSA stimulation (either 5MFU or 7MFU, depending on randomization).

As a secondary endpoint, the TRS score at 12 MFU under PSA stimulation is analyzed as a long-term parameter. Only some patients are stimulated in the PSA between 7MFU and 12MFU, since some patients might have chosen VIM stimulation after the randomization phase. Accordingly, a comparison between VIM and PSA stimulation at 12MFU might be possible (according to the group size).

For all other (secondary) endpoints evaluated for PSA-DBS, the difference between the score at 5/7MFU and the score at baseline is calculated.

For study question 2, the difference in tremor scores between PSA and VIM stimulation in each individual patient is calculated as the difference between TRS at 5MFU and 7MFU.

For all other (secondary) endpoints compared between PSA and VIM, the scores at 5MFU are compared with those at 7MFU, according to randomization group.

For study question 1, the mean reduction in tremor (TRS) due to PSA-DBS with its standard error and 95 % confidence interval is computed. The individual baseline and after-treatment values are tested against ”no reduction” using a paired *t* test. Similarly for SF-36, QUEST, and BDI-II, the mean change from baseline together with the corresponding 95 % confidence interval is calculated, and a paired *t* test is performed. A graphical display is used to examine the distribution of the data; in case of marked skewness or other non-conformity to test assumptions, the appropriate non-parametric tests are employed as a sensitivity analysis.

For study question 2, mean tremor at the end of the crossover period with PSA-DBS and VIM-DBS, respectively, is computed, with 95 % confidence intervals. A repeated measures analysis of variance, allowing for a period effect, is performed to quantify and test for a difference in mean tremor score between PSA and VIM in the crossover design. The mean difference between PSA and VIM with 95 % confidence interval is calculated from the model. Similarly for secondary outcomes, mean values under the two treatments are computed and compared using repeated measures analysis of variance.

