### Randomization

Block randomization with random varying block length is employed in order to generate balanced allocations over the two crossover groups. Numbered, sealed envelopes are produced, and these are opened sequentially for each enrolled patient. Due to the small sample size and since a crossover design is employed, it is not considered useful to stratify the randomization.

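### Filling missing items with the whole-group mode at 5MFU and 7MFU mixes PSA and VIM responses and shrinks the PSA-VIM contrast, by a few tenths of a TRS point on plausible assumptions

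*Protocol article*

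**What the plan says.** Under Handling of missing data, the protocol article sets an item-level rule and a score-level rule.

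- **Item level.** The trigger is "If only one component of a multiple component score (such as TRS part A, B, or C", or a corresponding part of QUEST or SF-36, being incomplete. The missing items are then "imputed using the most frequent (mode) response to this item in the entire group at the corresponding time point". Neither the stimulated target, nor the sequence, nor the patient's other answers enter the rule.
- **Score level.** "If a value measured after DBS is completely missing, the patient will be excluded from the main analysis of the corresponding endpoint". A sensitivity analysis brings these patients back by multiple imputation.

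The design is given elsewhere. Study procedure defines two sequences ("group 1: VIM-DBS followed by PSA-DBS; group 2: PSA-DBS followed by VIM-DBS") and two evaluation visits ("EV1 at 5MFU and EV2 at 7 MFU"). Randomization uses blocks to "generate balanced allocations over the two crossover groups". Under Statistical analysis, the post-PSA score for study question 1 is taken at "either 5MFU or 7MFU, depending on randomization", and the individual PSA-VIM difference for study question 2 "is calculated as the difference between TRS at 5MFU and 7MFU".

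**The concern.** In this crossover, fixing the visit does not fix the treatment. At 5MFU one sequence has just finished VIM and the other PSA; at 7MFU the roles are reversed. A mode over everyone at the visit therefore pools the two conditions that study question 2 compares. Two patients who miss the same item at the same visit get the same value even if one is on PSA and the other on VIM, so the filled part of the score carries no target difference.

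The rule also sets aside the best information on the patient's own severity, namely the completed items of the same part at the same visit. The filled value then enters the main analysis as if it had been observed. No planned sensitivity analysis clearly tests this, because the multiple imputation addresses values that are missing altogether.

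What is at stake is mainly the PSA-VIM contrast. The Discussion also offers a non-inferiority reading of it, with a margin of 9 points in favour of VIM.

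**Working it through.** **1. The plan's own figure.** Inputs from Sample size and power calculation: difference 9 points, power 80%, significance level 5% (taken as two-sided), correlation 0.5, SDs 10.1 (baseline) and 8.8 (after PSA). With SD 10.1 for both values, the SD of the difference is √(10.1² + 10.1² − 2 × 0.5 × 10.1 × 10.1) = 10.1. A paired t test by the noncentral t then needs n = 12 (power 80.2%), as stated. SD 8.8 for both gives n = 10, and one of each gives n = 11. A 20% margin gives 12 / 0.8 = 15, as stated. The point here does not depend on the sample size; the reproduction only supplies a scale.

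**2. Mechanism.** Let q be the share of a score that is filled, D the true PSA-VIM difference, and suppose that missingness does not depend on target. The filled share has the same expected value under both targets at a given visit, so with balanced sequences the expected contrast is D × (1 − q). If D = 0, nothing is lost.

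**3. Size.** The documents give no item-missingness rate, so 2, 5 and 10% are assumed. The simulations assume 12 patients (6 per sequence) and 20 items scored 0 to 4, missing at random. In the third and fourth columns the simulated difference is about 8.1 rather than 9 points, because items are capped at 4.

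| Assumed missingness | 9 × (1 − q), every missing item filled | Simulated loss, whole-group mode, every missing item filled | Same, mode within target | Simulated loss on a 9-point effect, only one part incomplete per score |
|---|---|---|---|---|
| 2% | 8.82 | 0.17 (2.1%) | 0.02 (0.3%) | about 0.2 |
| 5% | 8.55 | 0.44 (5.5%) | 0.07 (0.9%) | about 0.4 |
| 10% | 8.10 | 0.90 (11.1%) | 0.11 (1.4%) | about 0.6 |

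The last column applies the plan's trigger and is the relevant one. At higher missingness more scores have two or more incomplete parts, which the item rule does not reach, so the loss grows less than in proportion to missingness. How items are divided among the parts, and how scores with several incomplete parts are treated, are further assumptions. Other reasonable choices give smaller losses, so these figures are orders of magnitude.

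**4. Power.** With n = 12 and the SD of the difference held at 10.1, the noncentrality is effect / 10.1 × √12. It is 3.09 at 9 points and 3.02, 2.95 and 2.88 at 8.8, 8.6 and 8.4 points. Power goes from 80.2% to about 78, 77 and 75%.

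**5. Non-inferiority.** If PSA were truly worse by exactly the 9-point margin, the same shrinkage would put the expected estimate 0.2 to 0.6 points inside the margin.

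**6. Study question 1.** The planned reduction is 46.2 − 18.7 = 27.5 points, for which the plan needs n = 4. Baseline has no mixing of targets. As a rough guide, take the fill as the midpoint of two targets 9 points apart: the post-PSA score then moves by q × 4.5, or 0.09 to 0.45 points for q of 2 to 10%. That is at most 0.45 / 27.5 = 1.6% of the planned reduction.

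**The case against.** The best case for the plan is that the rule will rarely be used and usually errs on the safe side. The trigger is limited to one incomplete component. TRS is video-recorded for external rating, and the data centre checks the case report forms for completeness and queries discrepancies. Shrinkage toward zero is conservative for the stated hypothesis that PSA is superior, and the primary endpoint is PSA against baseline. All of this stands and is why the size is small. It does not make the rule sound: the non-inferiority reading is not protected by shrinkage, and the repair needs no new data.

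The wording might also rescue the plan. Entire group could mean one randomization sequence, in which case targets would not mix. But the rule names no sequence, whereas Statistical analysis does refer to the randomization group where it means one. All patients at the visit is the natural reading; if the other was meant, the sentence still needs correcting. Statistical analysis also speaks of sensitivity analyses that impute any missing values. That sentence concerns absent post-stimulation examinations and points to Handling of missing data, where multiple imputation is confined to completely missing values.

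Some stronger readings are tempting but unsupported:

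- A reader might infer that the rule can erase the PSA-VIM difference. At trial level that would need nearly every item to be filled.
- A reader might infer a large error for each filled item. That depends on invented item distributions and on which target is missing, and part of it would be the gap between a mode and a mean, not mixing.
- A reader might infer that tied modes are a consequence of the pooling. Ties are no rarer when the mode is taken within target.
- A reader might infer that severe patients are given milder values because their tasks cannot be rated. Nothing in the document says how such a task is scored or that it is left missing.

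**Conclusion.** The point holds, at a modest size. The protocol fixes an imputation rule that is blind to the treatment being compared, at the two visits from which the comparison is drawn. If PSA and VIM differ, the study question 2 contrast is pulled toward zero by roughly the share of items filled: about 0.2 to 0.6 of 9 TRS points at an assumed 2 to 10% item missingness with one part incomplete per score. This rests on the assumed missingness, on 20 items missing at random, and on missingness that is the same under both targets. On that last assumption there is no bias in the mean contrast when the targets are equal.

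The direction is conservative for superiority and favourable to PSA for non-inferiority if PSA is truly worse. The effect on the primary endpoint is small. The document does not support reading this as a threat to the trial's main conclusion.

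**What to change.** Replace the whole-group mode in Handling of missing data with item imputation that respects stimulation site and uses the patient's own completed items in the same part at the same visit. Two forms would do:

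1. A prorated part score from the completed items, with a stated minimum number of items. Parts below that minimum are treated as missing and go into the planned multiple imputation.
2. Extension of the planned multiple imputation to item level, with stimulation site and period in the model.

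The cost is one paragraph of analysis wording, with no further data or patients. Proration treats the items of a part as interchangeable, which is only approximate (TRS part C, for instance, combines eating, social distress and hygiene), and it still counts a filled value as observed. The second form avoids the latter fault but needs a model that is simple enough for about 12 patients. Under the first form, a few patients with mostly missing parts would move to the multiple-imputation analysis.

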### Randomization

Block randomization with random varying block length is employed in order to generate balanced allocations over the two crossover groups. Numbered, sealed envelopes are produced, and these are opened sequentially for each enrolled patient. Due to the small sample size and since a crossover design is employed, it is not considered useful to stratify the randomization.

### Implantation procedure

The general surgical procedure has been published in detail before. Patients are operated under local anesthesia with sedation (remifentanil and propofol).

In summary, after fixation of the stereotactic frame (CRW Stereotactic System, Integra Neurosciences, or Riechert-Mundinger frame), planning is performed on fused stereotactic CT/MRI images, with the Framelink (Medtronic Inc.) or STP 3.5 (Leibinger) planning station.

The trajectory is planned so that both VIM and PSA can be stimulated, with one electrode contact on the AC-PC level. Macrostimulation is performed in all patients. Microrecording is selected in a number of patients based on the surgeon’s preference. Implanted electrodes are quadripolar electrodes from Medtronic Inc. (model 3387 or 3389) or octopolar electrodes from Boston Scientific (model 616010).

Finally, the pulse generator (Activa PC, model 37601; Activa RC, model 37612, Medtronic, USA or Vercise, Boston Scientific, USA) is implanted subcutaneously in the infraclavicular or lateral abdominal region under general anesthesia.

### DBS programming

Directly after implantation and until 7MFU the activated electrode contact is determined by the study protocol (ICL, PSA, VIM or ICL, VIM, PSA), but the parameters can be freely chosen in terms of amplitude, frequency, and pulse width. However, all patients must be stimulated with constant current (mA), with a positive case and a single active cathode. In the crossover phase, at each programming visit, a monopolar review from 0 to 5 mA in 0.5-mA increments is performed. The amplitude with the best effect and fewest side effects is chosen for the final setting and is usually further adapted by the investigator during the programming visit before discharge. In general, a monopolar configuration with 60 μs and 130 Hz is chosen initially. In case a patient does not present a sufficient effect, the frequency and pulse width can be additionally modulated to improve the outcome.

If stimulation on a certain contact does not lead to a sufficient effect or intolerable side effects occur, and thus a change of the electrode contact or electrode configuration is inevitable, the corresponding crossover phase cannot be continued for ethical reasons. In this case the EV of the respective crossover phase must be performed immediately. After the end of the crossover phase, at 7MFU, the activated contact can be freely chosen.

### Blinding

During the crossover phase the study is performed in a double-blinded design. To ensure that neither the patient nor the physician is aware of the stimulation site (PSA or VIM), during the blinded crossover phase, each patient is seen by a blinded and an unblinded investigator (the latter usually being a study nurse). The unblinded study nurse performs all DBS programming during that phase. The physician decides according to clinical impression whether the stimulation parameters need to be modified (e.g., increase or decrease of amplitude or modulation of pulse width or frequency). The stimulation parameters and especially the activated contact (VIM or PSA) are documented in a separate file not accessible by the blinded physician. The blinded physician will be unblinded after all case report form (CRF) documentation of the crossover phase has been completed.

For the preoperative versus postoperative comparison of tremor suppression, all patients are videotaped and analyzed by an independent rater. The patients wear surgical caps before and after implantation, so that the rater cannot deduce the time point of data collection (i.e., preoperative versus postoperative) from, e.g., scars or short hair after implantation.

### Withdrawal from the study

In case of unexpected harm to the patient, insufficient compliance, or withdrawal of informed consent, a patient will promptly be excluded from further study treatment. In any case of premature withdrawal during the trial, the reasons for withdrawal must be documented in the CRF. The withdrawn subject will undergo a final examination (final visit) which must be documented.

### Safety

Implantation of electrodes in the PSA has so far not been associated with a higher risk for complications in these patients.

Adverse events (AEs)/serious adverse events (SAEs) are documented at the scheduled and unscheduled clinical visits. All incidents are reported to the regulatory authority. All safety-relevant events are promptly reported to the ethics committee and the safety monitor ([name], Department of Stereotactic Neurosurgery, University of Magdeburg, Germany).

### Quality assurance/monitoring

Monitoring is performed by the Clinical Trials Centre Cologne (CTC Cologne). Monitors inspect the study center regularly to ensure implementation of the study protocol and high quality of documentation. An initiation visit, four regular visits, and a close-out visit are performed. Original source documents are reviewed for verification of data in the CRF. For each patient the presence of written consent is checked and the inclusion and exclusion criteria are controlled.

### Documentation

All data relevant to the trial are documented soon after measurement by the responsible investigator in the CRF supplied, with signature.

### Data management

IT infrastructure and data management are provided by the CTC Cologne. The data management system is based on commercial trial software and includes a database. The trial database was developed and validated before data entry based on standard operating procedures at the CTC Cologne. All changes made to the data are documented in an audit trail. The trial software has a user and role concept that can be adjusted on a trial-specific basis. The database is integrated into a general IT infrastructure and safety concept with a firewall and backup system. The data are backed up daily. After completion and cleaning of data, the database is locked and the data exported for statistical analysis.

The arrival of CRFs at the CTC Cologne is documented and the CRFs are checked for completeness. Data entry staff members enter the data into a validated trial database using independent double data entry, and the data entered are compared and reconciled afterwards. Plausibility checks are also conducted in the database. Discrepancies and implausible values are clarified in writing between the data manager and the trial site. The trial site has to answer these queries without unreasonable delay. Further details will be specified in the data management manual.

### Data protection

The provisions of data protection legislation will be observed. It is assured by the sponsor that all investigational materials and data will be pseudonymized in accordance with data protection legislation before scientific processing.

Trial subjects will be informed that their pseudonymized data will be passed on in accordance with provisions for documentation and notification pursuant to sections 12 and 13 of the Good Clinical Practice (GCP) regulations to the recipients described there. Subjects who do not agree that the information may be passed on in this way will not be enrolled into the trial.

## Discussion

This study investigates the effects and side effects of deep brain stimulation of the PSA and — with the help of the randomized crossover — contrasts the outcome with that of VIM stimulation. Although this monocentric study will primarily serve as a pilot study for a larger, multicentric trial, we expect direct findings to improve treatment of future patients with ET, e.g., through a better understanding of the side effect profiles of the two target areas.

So far, results on PSA versus VIM stimulation are conflicting, and it is unclear whether the higher efficacy of PSA stimulation compared to VIM stimulation is sustained in the clinical setting when the amount of current and the amount and severity of stimulation-induced side effects might vary between the two target areas. Theoretically, the higher efficacy of PSA stimulation over VIM stimulation might potentially be neutralized by the use of stronger current in the VIM group or more frequent side effects in the PSA group, the latter limiting acceptable program settings in that target area.

Therefore, first, this study was designed such that patients are stimulated with constant current and not constant voltage to facilitate direct comparison of the amount of current (independent of the impedance of the electrode contacts) applied to the target area in both groups. Secondly, our study strongly focuses on stimulation-induced side effects in both target areas. If our study detects a lower rate of side effects in one of the two groups, this could relativize the result on tremor suppression. In fact, it might be the therapeutic window, which comprises effect and side effect, and not the mere amount of tremor suppression that is crucial for preference of one or the other target area. Thirdly, the required sample size for demonstrating non-inferiority of PSA-DBS compared to VIM-DBS is the same as that calculated to demonstrate superiority if the non-inferiority margin is set at a difference of 9 Essential Tremor Rating Scale (ETRS) points in favor of VIM-DBS (with the same values of standard deviation, alpha, and power and assuming a true difference of zero). Therefore, our study has an acceptable power to show approximate non-inferiority for the case that tremor suppression is similar with both treatments, but side effects are reduced under PSA stimulation.

The main strength of this study is the randomization of the patients in the double-blinded crossover phase. Potential limitations of the study are the relatively small sample size and a possible period effect of the crossover. The results of this pilot study need to be confirmed in a larger trial. Like other trials investigating the effects of DBS for the treatment of ET, there are some other DBS-specific methodological limitations. It is commonly accepted that, due to the direct and strong effect of VIM-DBS in ET patients, a truly blinded analysis of the preoperative to the postoperative state is probably impossible [2]. To circumvent this bias, we have designed a double-blinded analysis for the crossover trial comparing VIM and PSA, videotaping the preoperative and postoperative tremor scores for blinded analysis by an independent rater. Assuming that VIM and PSA stimulations do not differ strongly and predictably in effectiveness or side effects, the randomized crossover comparison is thus effectively blinded.

